## Abstract

**Background:**

Self-harm in young people is a public health concern connected with severe mental health problems, such as personality pathology. Currently, there are no specific evidence-based interventions available for young people who self-harm. Therefore, we developed *PRe-Intervention Monitoring of Affect and Relationships in Youth (PRIMARY)*, a smartphone-based intervention, co-designed by clinicians and young people with lived experience of mental ill-health. PRIMARY combines the Experience Sampling Method (ESM) with weekly report sessions. The study aims to examine the effectiveness of PRIMARY with regard to reducing self-harm, and improving emotion regulation and quality of relationships.

**Methods:**

This study is a multicenter, parallel groups, randomized controlled trial (RCT) comparing the PRIMARY intervention to a waiting list control group. PRIMARY comprises 28 consecutive days of questionnaires five times each day (i.e., ESM) and four weekly report sessions. Participants will comprise 180 young people referred for treatment to the participating Dutch mental healthcare institutions and (1) are aged 12 to 25 years, and (2) engaged in ≥ 1 act of self-harm in the past year. Participants are randomly allocated to a study group after screening in a 1:1 ratio by an independent researcher using computer-generated randomization sequences with stratified block randomization by age (12 to 15 years / 16 to 25 years). Staff will conduct assessments with all participants at baseline (Wave 1), after 28 days (Wave 2), and in a subsample after 10 weeks of subsequent specialized treatment (Wave 3). The primary outcomes are self-harm, emotion regulation, and quality of relationships. Secondary outcomes include patient and clinician satisfaction. Exploratory analyses of ESM data will examine the relationship between emotions, social relationships, and self-harm.

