We have developed *PRe-Intervention Monitoring of Affect and Relationships in Youth* (PRIMARY), which is a smartphone-based intervention for young people who self-harm. PRIMARY combines ESM with brief, weekly, one-on-one structured report sessions where the young persons’ ESM-responses are discussed. This paper presents the study protocol for a multicenter, randomized controlled trial (RCT), evaluating the effectiveness of the PRIMARY intervention compared with a waiting list control. If PRIMARY is found to be effective in enhancing emotion regulation and reducing self-harm, it would offer an accessible, easy-to-implement intervention for young people throughout the mental healthcare system.

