#### Main study parameters

**Self-Harming Thoughts and Behaviors.** Five questions were formulated to assess frequency and severity of self-harm, these are included in the Supplemental Material.

**Emotion Regulation.** The 18-item Difficulties in Emotion Regulation Scale (DERS-18) [47] is included. The DERS-18 comprises six subscales: ‘lack of emotional awareness’, ‘lack of emotional clarity’, ‘difficulty engaging in goal-directed behavior’, ‘impulse control difficulties’, ‘nonacceptance of emotional responses’, and ‘limited access to emotion regulation strategies’. Items are answered on a 5-point Likert scale. The scale has adequate construct and predictive validity, and good test-retest reliability [47].

**Quality of Relationships.** Participants fill out the 11-item version of the Network of Relationships Inventory – Behavior Systems Version (NRI-BSV) [48] regarding one parent and a best friend. The NRI-BSV comprises two subscales: ‘support’ and ‘negative interactions’. Items are answered on a 5-point Likert scale. The questionnaire was validated and the factor structure was confirmed [48].

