### Data analysis plan and power calculations

Analyses that cover effectiveness of PRIMARY will be performed according to a modified version of the *intention-to-treat* principle [71], which entails including all participants with at least one data point post-baseline regardless of their compliance during the study. This way, random selection in the sample will be guaranteed which ensures the most accurate conclusions following the analyses. In the following section, analyses will be outlined for each study objective (i.e., research question) as well as the required sample size to answer the research questions based on relevant power analyses and recent literature^1^. Multiple imputation will be considered if the amount of missing values is non-trivial. The randomization stratification variable of age and gender will be examined as covariates in the analyses described below. Other covariates, such as concomitant treatment, will also be considered.

To examine the effectiveness of PRIMARY, an ANCOVA-test will be used to compare data from Wave 1 and 2 by study group (study objective 1). Specifically, the following variables will be examined: emotion regulation, quality of relationships, and self-harm. To reach a power of 0.80, the power analyses run in G*Power 3.1 [72]^2^ and R [73], with an additional correction for the pre-test as a covariate, indicated a sample size of *n* = 48 per group to be necessary to detect a medium effect size (α = 0.05). Taking into account a drop-out of 10% (based on the feasibility study), a total sample size of *N* = 106 is necessary to answer this research question.

Regarding the effect of PRIMARY on the effectiveness of subsequent specialized treatment (i.e., HYPE), an ANOVA-test repeated measures with a within-between interaction will be applied to Wave 1, 2 and 3 including only those participants receiving HYPE treatment (study objective 2). To reach a power of 0.80, a sample size of *N* = 42-106 is necessary when considering a medium-large effect size (G*Power 3.1) [72]^1^. Taking into account the 10% drop-out from the feasibility study, a sample size of *N* = 46-118 is required (i.e., young people receiving HYPE treatment).

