## Discussion

The aim of the current multicenter randomized controlled trial is to examine the effectiveness of PRIMARY, a smartphone-based intervention for young people who self-harm and are awaiting further care at a mental healthcare institution. Specifically, its effect on emotion regulation and self-harming thoughts and behaviors will be examined. By using the ESM-methodology as both an intervention and measurement tool, the PRIMARY design is new within the field. Specific attention was given to increasing the feasibility of the study by co-designing PRIMARY with young people with lived experience of mental ill-health, including insights from earlier ESM-studies, and by conducting a feasibility study.

This study strives to evaluate an evidence-based, low-cost, structured intervention which can be offered to those seeking help in the future. Furthermore, the ESM-data allows for a detailed examination of the processes underlying self-harm, which will contribute to theoretical knowledge regarding this behavior.

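### Three unranked primary outcomes share a sample size built on a single comparison at an undivided alpha of 0.05, with no rule for what counts as success

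*Protocol article*

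**What the plan says.** The Abstract (Methods) lists the outcomes without ranking them: "The primary outcomes are self-harm, emotion regulation, and quality of relationships". The Objectives section gives the same three under the first objective. The section on the data analysis plan and power calculations applies ANCOVA to Wave 1 and Wave 2 data by group and adds: "Specifically, the following variables will be examined: emotion regulation, quality of relationships, and self-harm".

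The sample size for this objective follows directly. It begins "To reach a power of 0.80, the power analyses run in G*Power 3.1" and concludes that 48 are needed "per group to be necessary to detect a medium effect size (α = 0.05". With 10% drop-out the total is 106, described as what this research question requires. The Abstract plans 180 participants.

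Two narrative passages name fewer outcomes. The end of the Background, under the heading on the smartphone-based intervention, says "If PRIMARY is found to be effective in enhancing emotion regulation and reducing self-harm" and goes on to what would then be on offer. The Discussion restates the aim as "its effect on emotion regulation and self-harming thoughts and behaviors will be examined". Neither mentions relationships. The Background and Discussion parts of the Abstract name all three outcomes.

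Under the main study parameters, the NRI-BSV has two subscales and is completed "regarding one parent and a best friend". The DERS-18 has six subscales. Self-harm is covered by five questions on frequency and severity. The article does not say which score represents each outcome.

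**The concern.** An alpha and a power describe a decision. The decision here rests on three outcomes, but the calculation describes one test of one outcome. To connect the two, the plan has to say whether one, two or all three outcomes must be significant for PRIMARY to be called effective.

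Without that rule, the stated pair of 0.05 and 0.80 can fail in either direction. If one success is enough, the error rate exceeds 5%. If all are needed, the power at the stated size is below 80%. A rule chosen after the results are known would leave the conclusion open to selection. That matters more here because staff are not blind to allocation.

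**Working it through.** **Inputs from the article.** Three primary outcomes; alpha 0.05; power 0.80; medium effect; correction for the pre-test as covariate; 10% drop-out; 1:1 allocation; 180 planned.

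**Assumptions.** The article does not give sidedness, the numerical effect size or the baseline correlation. I take two-sided tests, d = 0.5 and r = 0.5, because these reproduce the stated number. The correlation between outcomes is not given either, so I show 0 and 0.5.

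**Reproducing the stated size.** A two-sided t-test with d = 0.5, alpha 0.05 and power 0.80 needs 63.8, so 64 per group. The ANCOVA correction gives 64 × (1 − 0.5²) = 48. Other values of r miss: 0.4 gives 54 and 0.6 gives 41. For drop-out, 96 × 1.1 = 105.6, so 106 (96/0.9 would give 107). The stated figure is therefore what one comparison at the full 0.05 requires.

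**If any one outcome suffices (no true effect on any).** For k independent tests the error is 1 − 0.95^k. The correlated figures come from an equicorrelated normal integral.

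| Tests | Two-sided, independent | Two-sided, correlation 0.5 | Favourable direction only |
|---|---|---|---|
| 3 | 1 − 0.95³ = 14.3% | 12.5% | 7.3% to 6.3% |
| 6 | 1 − 0.95⁶ = 26.5% | 20.7% | 14.1% to 10.4% |

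The row for six is an illustration only: one self-harm score, one DERS-18 total and 2 × 2 = 4 NRI-BSV scores. The article does not fix that count.

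**If all must succeed, at 48 per group.** Each test has power 0.80.

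- Two outcomes: 0.80² = 0.64 if independent, 0.69 at correlation 0.5.
- Three outcomes: 0.80³ = 0.51 if independent, 0.61 at correlation 0.5.

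**At the planned 180.** After 10% loss, 180 × 0.9 = 162, or 81 per arm. The covariate-adjusted effect is 0.5/√(1 − 0.25) = 0.577.

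| Alpha per test | Power, 48 per arm | Power, 81 per arm |
|---|---|---|
| 0.05 | 0.80 | 0.955 |
| 0.05/3 = 0.0167 | 0.65 | 0.89 |
| 0.05/6 = 0.0083 | 0.55 | 0.84 |

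Joint power with 81 per arm at 0.05 each, if independent, is 0.955² = 0.91 for two outcomes and 0.955³ = 0.87 for three. Positive correlation raises both.

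**Size needed at alpha/3.** 64 per group, 128 in total, and 128/0.9 = 143 with drop-out. This exceeds 106 and lies within 180.

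**The case against.** The strongest reply is about scope. This is a journal article, and a multiplicity procedure or the choice of score per instrument is commonly left to an analysis plan, which is not shown. The text of the footnotes attached to the power analyses is not shown either. That stands: the absence of a named correction is not itself a fault. What remains is what the article does state, namely three unranked primary outcomes and a sample size for that three-outcome question based on one test at 0.05. A correction set elsewhere would still conflict with that power statement.

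A reader might infer that each of about six scores will be tested at 0.05, giving a 12-26% chance of a false claim. The article does not support this. It states no any-one-counts rule, alpha for this objective appears only in the sample-size sentence, and six is an inferred count. Those percentages also include apparent harm; false claims of benefit are about half as frequent.

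A reader might also take the Background sentence as the success rule. It is motivation, not a decision rule, and the Abstract names all three outcomes. If it were read literally as requiring both outcomes, the error would be at most 5% and the shortfall would be in power.

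Finally, the low joint power belongs to 48 per group. At the planned 180, even an all-three rule keeps more than 80% under the assumptions above. That stands in full.

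**Conclusion.** The point holds in a limited, conditional form. Alpha 0.05 and power 0.80 at 48 per group describe one comparison and do not jointly describe either natural decision on three primary outcomes. Under an any-one rule the two-sided family-wise error is about 12-14%, and higher if several NRI-BSV or DERS-18 scores are each tested. Under an all-three rule the joint power at that size is about 0.51-0.61. The differing lists of outcomes in the narrative sections are loose wording that leaves the rule less clear; they are not a competing rule.

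The error rates assume no true effect on any outcome and correlations between outcomes of 0 to 0.5. The power figures assume d = 0.5 and a baseline correlation of 0.5 for every outcome, including self-harm; the article gives neither number. The planned 180 is large enough to absorb the correction under those assumptions, so this is a defect in the stated decision rule and power statement, not in the planned number of participants.

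**What to change.** 1. Name one score for each primary outcome, chosen from those collected at Wave 1 and Wave 2. For self-harm, check this against Table 1, which as read here marks the self-harm questions at screening only.
2. State one success rule, and use the same list of outcomes in the Abstract, the Background, the Objectives, the analysis section and the Discussion.
3. Control the family-wise error at 0.05 across the three scores, by Holm or by testing in a pre-specified order. If the rule chosen is that all must succeed, no division of alpha is needed, but joint power should be reported.
4. Replace the power statement for objective 1 with one for the planned 180 under the chosen rule. With alpha/3 it is about 0.89 per outcome at 81 per arm, against 0.65 at 48 per group. State the effect size and baseline correlation assumed.

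The cost is a change of wording and, under Holm, a stricter threshold for at least the first outcome tested. No extra participants are needed. The article reports data collection as ongoing, so the rule should be fixed before outcome data are examined by group.

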**Discussion:**

The results of this trial will clarify whether an innovative smartphone-based intervention is effective for reducing self harm and improving emotion regulation and the quality of social relationships. It has the potential to fill a treatment gap of interventions specifically targeting self-harm. If proven effective, it would provide an accessible, easy-to-implement, low-cost intervention for young people. Furthermore, the ESM-data will allow detailed analyses into the processes underlying self-harm, which will contribute to theoretical knowledge regarding the behavior.

**Trial registration:**

ISRCTN42088538 (10.1186/ISRCTN42088538), retrospectively registered on the 26th of October 2022.

**Supplementary Information:**

The online version contains supplementary material available at 10.1186/s12888-023-05301-x.

## Background

Self-harm is common in young people and represents a major public health challenge [1–3]. Self-harm is defined as all intentional acts of self-injury or self-poisoning, irrespective of the type of motive [4]. Self-harming behavior is associated with problems in emotion regulation [5], enduring psychosocial problems [6], and shows a clear connection to severe mental health problems, such as depression, anxiety, substance use, personality pathology and suicidality [7–9]. Hence, early detection and intervention for self-harm are crucial. However, treatment for self-harm is often only available within specialist, psychotherapeutic programs, such as Dialectic Behavioral Therapy (DBT) and Mentalization Based Treatment (MBT), which target a range of difficulties [10, 11]. These programs entail complex and lengthy interventions, requiring extensive staff training and financial resources [12]. Hence, there is a need for simpler and ‘scalable’ evidence-based interventions that are specifically designed for self-harm. Such interventions might be more easily implemented across the healthcare system [13], making them available to more young people [12], and are likely to be more cost-effective [14].

### Self-harm

Beyond the immediate adverse effects of self-harm, like tissue damage [15], self-harm is a marker for an increased risk of developing various mental health problems [16, 17]. Given that the chance of repetition of self-harm within 12 months after the first incident increases with every prior act, with up to 70% in the case of four previous acts [18], it is important to intervene as early as possible to prevent persistent and profound problems. severe pathology. Recurrent self-harm is associated with severe psychopathology, such as borderline personality disorder (BPD) [19]. Studies have shown that over 40% of young people who self-harm during adolescence and have received mental healthcare, go on to receive a diagnosis of BPD in adulthood [20]. Therefore, interventions aimed at diminishing self-harm might also function as early intervention for those at risk of developing severe psychopathology, by targeting underlying problems of emotion regulation and interpersonal functioning [21].

Even though evidence-based treatments specifically aimed at preventing the recurrence of self-harm in young people engaging in the behavior are not yet available [22], positive effects of broader treatment programs provide important insights into the mechanisms underlying the reduction of self-harm. First, actions aimed at long-term improvement of psychosocial functioning have been found to be beneficial (e.g., re-orienting to a more positive future, reassessing one’s place in the social world; [23]. Second, actions aimed at breaking the association between an individual’s psychological or social state and the act of self-harm, i.e. ‘breaking the chain’, are important for short term change [23]. This includes strategies to manage immediate thoughts and feelings when the urge to self-harm arises, including improving emotion regulation, family support, and self-esteem [24]. Preceding the employment of such strategies, and essential to change harmful behavior, is gaining insight or awareness of problem areas and triggers [25, 26]. As the median time between the first thought of self-harm and the actual act has been found to be 35 h in some groups [27], there seems to be a ‘window of opportunity’ for the young person to recognize the separate steps of the ‘chain’ leading up to the act of self-harm. Subsequently, suggestions for more helpful coping techniques might guide the individual towards alternative strategies. Given that self-harm often fulfills the function of regulating emotions and interpersonal contexts [21], enhancing a young person’s insight into these areas seems especially important.

### Smartphone-based intervention

Help-seeking among young people is impeded by stigma, embarrassment, trouble recognizing symptoms, and a preference for self-reliance [28]. When young people do seek treatment, they are often faced with long waiting times within the mental healthcare system, which can demotivate them [29, 30]. This is especially problematic in the context of self-harm, given the direct and long-term adverse effects of the behavior. A smartphone-based intervention for young people who self-harm might contribute to overcoming the constraints of the current system, such as limited availability of clinicians [31]. Such an intervention would be self-directed and readily accessible for young people in their day-to-day lives.

The Experience Sampling Method (ESM) is a smartphone-based approach that asks people to fill out questions via their smartphone on multiple occasions during the day, for example regarding their feelings and behaviors [32]. ESM has been used to study the mechanisms underlying self-harm, which has led to the insight that heightened negative affect typically precedes the behavior [27, 33]. The ESM-methodology has thus far primarily been employed as a research tool for assessing self-harm. However, the act of systematically monitoring and registering feelings and behaviors might also be an intervention in and of itself, as it promotes reflection and facilitates the discovery of patterns of feelings and behavior [34]. The application of ESM as an intervention has already been recognized in the field of depressive disorders, where ESM is now studied as an add-on intervention to outpatient treatment programs [35, 36]. More recently, the use of ESM as a stand-alone smartphone-intervention has been demonstrated to be associated with positive mental health outcomes in young people in the community [37].

ESM has been posited as a promising framework for an intervention targeting self-harm [38]. Preliminary evidence suggests a possible decline in the frequency of the behavior when using smartphone-based interventions [39]. However, there is large variation in the type of smartphone-based interventions available and randomized controlled trials (RCTs) are needed to rigorously examine their effectiveness. Furthermore, co-designing an ESM-intervention in partnership with people with lived experience of mental ill-health enhances the fit of the intervention to the target group [40].

We have developed *PRe-Intervention Monitoring of Affect and Relationships in Youth* (PRIMARY), which is a smartphone-based intervention for young people who self-harm. PRIMARY combines ESM with brief, weekly, one-on-one structured report sessions where the young persons’ ESM-responses are discussed. This paper presents the study protocol for a multicenter, randomized controlled trial (RCT), evaluating the effectiveness of the PRIMARY intervention compared with a waiting list control. If PRIMARY is found to be effective in enhancing emotion regulation and reducing self-harm, it would offer an accessible, easy-to-implement intervention for young people throughout the mental healthcare system.

### Objectives

The first objective of this RCT is to determine whether PRIMARY, compared to a waiting list control, is effective in improving the following outcomes: self-harm, emotion regulation, and quality of relationships. To this end scores at baseline (Wave 1) and at the end of the intervention phase (Wave 2) will be compared. The second objective is to examine the effectiveness of PRIMARY combined with subsequent specialized treatment in the early intervention program Helping Young People Early (HYPE) [41] in improving the outcomes for young people with borderline personality pathology. Scores on the specified outcome variables after 10 weeks of HYPE treatment (Wave 3) will be compared to scores at baseline (Wave 1) and at the end of the intervention phase (Wave 2) for participants who attended HYPE. The third objective is to investigate the associations between emotions, relational support and conflict, adaptive coping strategies, and self-harm using individual-level ESM data. The fourth objective is to examine the participants’ and clinicians’ satisfaction regarding the use of PRIMARY. This will be examined at the end of the intervention phase (Wave 2).

